## Abstract

**Background:**

Child abuse and postnatal depression are two public health problems that often co-occur, with rates of childhood maltreatment highest during the first year of life. Internet-based behavioural activation (iBA) therapy has demonstrated its efficacy for improving postnatal depression. No study has examined whether the iBA program is also effective at preventing child abuse. This study aims to investigate whether iBA improves depressive symptoms among mothers and prevents abusive behaviours towards children in postpartum mothers in a randomized controlled trial, stratifying on depressive mood status. The study also evaluates the implementation aspects of the program, including how users, medical providers, and managers perceive the program in terms of acceptability, appropriateness, feasibility, and harm done.

**Methods:**

The study is a non-blinded, stratified randomized controlled trial. Based on cut-off scores validated on Japanese mothers, participants will be stratified to either a low Edinburgh Postnatal Depression Scale (EPDS) group, (EPDS 0–8 points) or a high EPDS group (EPDS ≥9 points). A total of 390 postnatal women, 20 years or older, who have given birth within 10 weeks and have regular internet-access will be recruited at two hospitals. Participants will be randomly assigned to either treatment, with treatment as usual (TAU) or through intervention groups. The TAU group receives 12 weekly iBA sessions with online assignments and feedback from trained therapists. Co-primary outcomes are maternal depressive symptoms (EPDS) and psychological aggression toward children (Conflict Tactic Scale 1) at the 24-week follow-up survey. Secondary outcomes include maternal depressive symptoms, parental stress, bonding relationship, quality of life, maternal health care use, and paediatric outcomes such as physical development, preventive care attendance, and health care use. The study will also investigate the implementation outcomes of the program.

**Discussion:**

The study investigates the effectiveness of the iBA program for maternal depressive symptoms and psychological aggression toward children, as well as implementation outcomes, in a randomized-controlled trial. The iBA may be a potential strategy for improving maternal postnatal depression and preventing child abuse.

**Trial registration:**

The study protocol (issue date: 2019-Mar-01, original version 2019005NI-00) was registered at the UMIN Clinical Trial Registry (UMIN-CTR: ID UMIN 000036864).

## Background

Child abuse is a challenging issue in public health as it affects the physical, psychological, and social health outcomes of individuals for a lifetime [1–9]. From a societal perspective, child abuse imposes a substantial financial burden on societies as it creates high direct and indirect costs in low, middle, and high-income countries [10–12]. Existing research has identified the following characteristics as being associated with a higher risk for child abuse: parental depression, anxiety and anger-hyperactivity, parent stress, poor parent–child interactions, and low social support [13]. However, there is presently no solution for how to prevent child abuse right after birth.

Postnatal depression is another critical problem closely related to child abuse [14, 15]. Depression is the leading cause of disease-related disabilities among women [16, 17]. Previous studies indicated that women with postpartum depression were at higher risk for lower physical and psychological health, substance abuse, and suicidal behaviours [18–22]. Child abuse and postnatal depression often co-occur, and the rate of childhood maltreatment is highest during the first year of life [23, 24]. Children born to depressed mothers were at higher risk for prematurity, delayed physical, motor, and cognitive development [22]. Moreover, postnatal depression among mothers was associated with a significantly increased risk for harsh parenting, physical and psychological abuse [14, 15, 25–27].

Previous evidence has demonstrated that cognitive behavioural therapy (CBT) is effective for improving depressive symptoms among postnatal women [28–33], and emerging evidence has shown that it also reduces maternal stress [34, 35]. Behavioural activation (BA) is a simple but effective psychotherapy that follows the basic CBT principles but does not include cognitive restructuring. The practical principles of BA may be of particular use for postnatal women, who face multiple competing demands on their time and attention. Further, the parsimonious, simple nature of BA supports its straightforward application with a wide range of mental health providers, contributing to its promise as a highly scalable intervention [13]. Moreover, as BA facilitates participants to engage in positive behaviours and works on problem-solving strategies when barriers to implementation of these behaviours are encountered, it may increase positive parent–child interactions, possibly enhancing the bonding relationship between mothers and children and improving child outcomes. In a large study of BA in postnatally depressed mothers who were also randomly assigned to receive either relaxation or a video-feedback parent–child intervention, both conditions resulted in improved cognitive, behavioural and attachment outcomes for the child at 2 years of age [36]. These results suggest that BA may help to support the parent–child relationship underpinning attachment, possibly preventing parental abusive behaviours toward their children.

Internet-based psychotherapy has become an alternative approach to face-to-face psychotherapy or other interventions due to its strengths in accessibility, reach, and cost effectiveness [28, 32, 37–41]. These approaches have gained widespread application during the COVID-19 pandemic. Users can choose their device, time, and place to receive the program depending on their needs. Providers of the program, on the other hand, can deliver the application to the mass target population with fewer human resources and lower cost. A number of studies have now demonstrated that internet-based cognitive behavioural therapy (iCBT) [38, 42], which contains internet-based behavioural activation (iBA) is an effective treatment for prenatal depression, and that iBA itself is an effective treatment for postnatal depression [31, 32].

Internet-based psychotherapy not only reduces practical barriers to access for users but may also reduce psychological barriers. Previous evidence has shown that many women with postnatal depression struggle with stigmatization, and this can be an obstacle for health care providers attempting to connect depressed mothers with medical care [43, 44]. In qualitative studies of iBA for postnatal depression, mothers who reported struggling with stigma stated that they found internet intervention more acceptable than face-to-face intervention [45]. We expect that internet-based interventions including smartphones, which have become such standard communication tools, would make it easier for mothers in need to seek care for their mental health. Internet-based psychotherapy, however, has its own challenges. Many studies have described the high attrition rate of internet-based psychotherapy, ranging from 9.7 to 78.9% of the participants, as a weakness of web-based interventions [40, 46]. Internet-based interventions demonstrated improved retention rates with human support [28, 32, 41, 47–49]; however, the adequate intensity of support needed to achieve the goal is still unknown. As the implementation of the program involves not only the users but also medical providers and hospital managers, it is essential to understand how the program is perceived in terms of acceptability, appropriateness, feasibility, and potential harm perceived by these stakeholders.

## Methods/design

### Objectives

The study is a 6-month follow-up stratified randomized controlled trial at multiple medical centres. A web-based behavioural activation program for smartphones with therapist support will be developed for postnatal mothers in Japan, based on a previous study [32]. The aims of the study are as follows:
To investigate the effect of an internet-based behavioural activation program on improving depressive symptoms and preventing abusive behaviours toward their children as co-primary outcomes, as well as parental stress, bonding relationship, health-related quality of life (QOL), and child developmental measures as secondary outcomes.To investigate how the medical and social characteristics of participants influence implementation aspects (acceptability, appropriateness, and feasibility). We have set two co-primary outcomes in this trial, as the effects on both mothers and children are equally important. The hypotheses of the study are as follows:

(H1) The web-based behavioural activation program for smartphones will significantly improve depressive symptoms 24 weeks after the initiation of the program among postnatal mothers with EPDS scores ≥9 points in the intervention group as compared to those in the TAU group; and.

(H2) The smartphone-based behavioural activation program will significantly prevent abusive behaviours toward children at 24 weeks after the initiation of the program among all the postnatal mothers in the intervention group as compared to those in the TAU group.

### Study design

The study is a non-blinded, parallel group, stratified randomized controlled trial. Based on the most recent score of the Edinburgh Postnatal Depression Scale (EPDS) at recruitment, participants will be stratified to either low EPDS group (EPDS 0–8 points) or high EPDS group (EPDS ≥9 points) after completing the baseline survey. The threshold of 8/9 points was determined fit according to the previous validation studies conducted in Japan [50, 51].

The allocation ratio of the intervention group to the control group is set as 1:1. Participants will be asked to answer the online follow-up surveys at 12 and 24 weeks after the initiation of the program. The protocol of the study was registered at UMIN Clinical Trial Registry (UMIN-CTR: ID UMIN 000036864). As of February 2021, we are in the process of recruiting participants. The study protocol follows the Standard Protocol Items for Randomized Trials (SPIRIT) guideline checklists.

### Study setting

The study will be conducted in the department of Obstetrics and Gynecology at two tertiary care hospitals that provide maternal and foetal intensive care in Yokohama, Japan.

### Inclusion criteria

Age ≥ 20 years old at recruitment (Age of adulthood is 20 years or older in Japan).Postnatal women who had given birth within 10 weeks of recruitment.Have regular internet-access via smartphones or other internet devices.Currently living with the new-born baby.Fluent in Japanese (Able to understand the content and work on the program).

### Exclusion criteria

Current suicidal intent at recruitment.Currently not living with the new-born baby for any reason, including if the baby is still receiving care in the neonatal intensive care unit.Currently receiving public livelihood assistance or public assistance for delivery cost.

### Procedure

The flow chart of participants is presented in Fig. 1. Women who have given birth and arrive at the study sites for postnatal visits (usually at 4 weeks after delivery), and fulfilled the eligibility criteria, will be considered as possible candidates for recruitment. Potential candidates will receive handouts with brief information on our research study from their health care providers (medical doctor, nurse, midwife, or medical assistants). If they are interested in participating in the study, they will be given access to a Quick Respond code. This machine-readable optical barcode can connect to our information site on the internet and register their e-mail addresses for further information. If candidates agree to participate after reading the full information on our study, they will go through the online informed-consent process by confirming that they have read and understood the statements and clicking the “agree” button. Consenting participants will be asked to answer a baseline online survey (T1). Participants will then be allocated to either an intervention group or a treatment as usual (TAU) control group, stratified according to EPDS scores at recruitment (low EPDS: 0–8 points, high EPDS ≥9 points), and hospital codes. To ensure allocation concealment, research assistants will register group codes into the program using the block randomization sheet created by a biostatistician.

**Fig. 1 Fig1:**
[figure not shown]
Flow chart of participants

This study also conducts a short survey on the implementation of the program with medical providers and hospital managers of the study during the recruitment period. The providers and hospital managers will be asked to browse the content of the program with their own smartphones and answer the short survey consisting of implementation and usability scale outcomes.

### Intervention program

The intervention program (SmartMama) is developed based on the UK behavioural activation program for postnatal depression (Client manual: Self-help booklet for postnatal depression by [name] [52]), adjusted for Japanese postpartum mothers who use smartphones [30]. The program consists of 12 weekly online sessions (each session requires 30 min) with online assignments and feedback from trained therapists during the course.

The contents of the program are shown in Table 1. In Sessions 1 and 2, participants learn about basic concepts of behavioural activation—that mood, feeling, and behaviours are closely related. They practice how to track their mood, feelings, and actions using a mood diary. In Sessions 3 and 4, participants learn about Triggers–Reactions–Avoidance Patterns (TRAPs) model, how the trigger event leads to a certain mood, often causing avoidance behaviours among participants. Participants break down the patterns of the situations in which they felt stuck, apply the TRAP model to explain their cases, and understand that their actions and mood are closely linked. In Sessions 5 and 6, participants learn to develop alternative coping strategies to handle the situations and shift from avoidance patterns to alternative coping. In Sessions 7 and 8, participants learn about strategies for effective communication and to ask for support. In Sessions 9 and 10, participants identify their goals of being good-enough mothers and turn their avoidance behaviours into alternative coping. In Sessions 11 and 12, participants learn about strategies to stay well, recognize their warning signals, and prepare for the future.

**Table 1 Tab1:** The contents of the behavioral activation therapy program

Sessions	Title	Contents
0	Introduction	Introduction on changes that occur in perinatal periods that affect your activities
1	Understanding the depression cycle	Learning about relationship between your mood and behaviours, and exercise to fill out the mood diary.
2	Self-monitoring, self-care	Learning about self-monitoring skills.
3	Identifying the patterns to get stuck in you depressive mood	Understanding the Triggers-Reactions-Avoidance Patterns (TRAPs) model.
4	Case study	Case studies on how a trigger event induces feeling (reaction), causing avoidance pattern. Writing about your own case using a TRAP model.
5	Altenative coping stratigies	Looking for althernative activities as a mother
6	Case Study	Case studies on using alternative coping. Analyse your own case to come up with althernative behaviours.
7	Support and communication	Understanding your need for support and how communication needs to be changed during perinatal period.
8	Communication strategies	Learning communication strategies to ask for help and support in a comfortable way.
9	Being a “good-enough” mom	Identifying your own “mummy goals” and using althernative coping strategies to meet them.
10	TRAPs aroug being a good enough mom	Looking at your TRAP case and how to turn into altenative coping behaviours.
11	Staying well	Looking back over the course and identify the strategies that were effective and helpful.
12	Planning ahead	Identify your warning signals and plan your strategies to feel better.

### Intervention group

Participants in the intervention group will be asked to work on 12 weekly sessions of the online application-based behavioural activation programs, as described in the previous section. Each week, participants in the intervention group will receive e-mail reminders that a new session has become available. Further, they will be asked to answer short screening questionnaires on their depressive symptoms each week. If the participants present with severe depressive symptoms and suicidal thoughts, alert messages and information on mental health care will appear on the screen, as well as automatically notifying investigators of the information. If participants have questions about the program, they can ask the therapists within the program. They will receive answers within 1–2 days. Participants are allowed to receive treatment as usual, including inpatient or outpatient consultation, medication, or psychotherapy during the study period.

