### Control (TAU) group

Participants in the TAU group receive weekly messages and will be asked to answer short screening questionnaires on their depressive symptoms each week. Similar to the intervention group, alert messages and information on mental health care will be shown if the participants present with severe depressive symptoms or suicidal thoughts. They are also allowed to receive treatment as usual, including inpatient and outpatient medical care.

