#### Sample size calculation

As the study has two co-primary outcomes, we calculated each sample size needed to improve the depressive symptoms of mothers and to prevent abusive behaviours toward children based on the effect size from a previous study.

The study reported the effect size of the internet-based behavioural activation for postnatal depression as d = 0.55 [32]. With a significance level of 0.05, the statistical power of 80%, and a follow-up rate of 85%, the sample size needed to detect efficacy for postnatal depression in the high EPDS group is 128 participants (64 participants for each arm). (Sample size calculation was carried out using the G*Power 3.1.9.2.)

No previous study examined the effect of iBA for preventing child abuse, so we used the effect size d = 0.56 of cognitive behavioural therapy for anger from a randomized controlled trial [64]. We estimated the effect size of the iBA for psychological aggression as d = 0.50 for the high EPDS group based on the previous study [64], and d = 0.40 for the low EPDS group. With a significance level of 0.05, the statistical power of 80%, and a follow-up rate of 80%, the required sample size is 150 participants for the high EPDS group (75 participants per arm) and 240 participants for the low EPDS group (120 participants per arm).

Finally, we expected the sample size needed to detect the change in both depressive symptoms and abusive behaviours would be 150 participants for the high EPDS group and 240 participants for the lower EPDS group.

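### The weekly safety alert has two inconsistent triggers: both conditions required in the intervention arm, either one sufficient in TAU

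*Protocol article*

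**What the plan says.** The protocol article describes the weekly screen and its alert once for each arm, in adjacent sections.

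- **Intervention group section:** "If the participants present with severe depressive symptoms and suicidal thoughts, alert messages and information on mental health care will appear on the screen". The section names a further consequence of the same trigger: "as well as automatically notifying investigators of the information".
- **Control (TAU) group section:** "Similar to the intervention group, alert messages and information on mental health care will be shown" under the condition that follows, namely that the alert "will be shown if the participants present with severe depressive symptoms or suicidal thoughts".

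In both arms the alert follows a short questionnaire on depressive symptoms answered every week. The article does not define the trigger anywhere else. The Study design section adds that, as of February 2021, "we are in the process of recruiting participants".

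**The concern.** The TAU section refers back to the intervention arm, so the reader expects one rule. Two are given. With *and*, a woman must meet both conditions before anything happens. With *or*, one condition is enough. The two rules cannot both describe the same alert.

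The pattern that matters most is suicidal thoughts in a woman whose symptom score is not severe. A safety rule should not miss her, and the intervention-arm wording, taken at face value, does. What is at stake is participant safety and the same safety handling in both arms. It is not the statistical inference.

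**Working it through.** The article gives no figure to reproduce, so the check is a comparison of the two texts.

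**Inputs**

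1. Intervention-arm trigger (Intervention group section): severe symptoms *and* suicidal thoughts. The stated consequences are an on-screen alert, information on care, and automatic notice to investigators.
2. TAU trigger (Control (TAU) group section): severe symptoms *or* suicidal thoughts. The stated consequences are an on-screen alert and information on care.
3. Link between the arms: "Similar to the intervention group, alert messages and information on mental health care" introduces the TAU rule, so one common alert appears to be meant.

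**The two rules applied to each possible screen result**

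| Severe symptoms | Suicidal thoughts | Intervention wording (*and*) | TAU wording (*or*) | Same result? |
|---|---|---|---|---|
| No | No | No alert | No alert | Yes |
| No | Yes | No alert | Alert | **No** |
| Yes | No | No alert | Alert | **No** |
| Yes | Yes | Alert | Alert | Yes |

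The rules differ exactly when one condition is present without the other. In both of those rows the intervention wording is the less protective one. Because the notice to investigators depends on the same condition, it lapses with the alert.

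**Does another section settle it?** No.

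- The Exclusion criteria remove women with current suicidal intent, but only at recruitment. Thoughts that arise later, or that fall short of intent, are not covered.
- The Intervention program section provides "feedback from trained therapists during the course". The Intervention group section adds a channel for questions to therapists and leaves usual care open. None of these is described as a response to a positive weekly screen.

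**How many women?** That would need the frequency of each single-condition pattern among weekly screens. The article gives neither frequency, so no count follows from it.

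**The case against.** The strongest reply is that the article resolves the matter itself. The TAU section ties its alert to the intervention arm's, and *or* is the clearer statement of a shared rule. The *and* can be read as a list of the things that prompt alerts, not as a strict conjunction. Neither sentence names the questionnaire, defines severe, or gives a cut-off, so neither is an operating specification. Those details may properly sit in the full protocol.

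Most of this stands. Loose drafting is the likelier explanation, and the missing cut-offs are not a defect of a condensed article. The point here is different: two rules are stated, and they conflict. A reader of the article cannot tell with certainty which one protects women in the intervention arm.

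A second reply is that the alert is not the only contact. Intervention-arm women have therapist feedback, the question channel and usual care. This is true and it lowers the stakes, but it does not replace a response to the screen.

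Three stronger readings are tempting, and the documents do not support them:

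- **That the narrower rule is operating now.** Recruitment was already under way when the article was written, so the article describes a running system and is unlikely to be what that system was built from. Nothing in it shows that the system uses *and*.
- **That half the trial is affected.** The planned totals are "150 participants for the high EPDS group and 240 participants for the lower EPDS group", which at 1:1 allocation put 75 + 120 = 195 of 390 women in the intervention arm. That is the size of an arm, not a count of women missed. Likewise, disagreement in two of the four table rows is true of any *and*/*or* pair and is not a rate.
- **That investigators are not told about alerts in TAU.** The Control (TAU) group section neither states nor excludes this. In a condensed article that is an omission and adds no weight.

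**Conclusion.** The inconsistency is real: one shared safety alert is given two different triggers in adjacent sections, and no other text decides between them. It is probably a drafting slip, and the documents do not show that the arms are handled differently in practice. The harm described above depends on the literal reading of the intervention-arm sentence.

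Its size in women or screens cannot be estimated from the article. Sample size, alpha and the planned analysis are untouched. It still deserves correction, because the rule concerns suicidal thoughts in postnatal women and the literal wording errs in the less safe direction.

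**What to change.** In the Intervention group section, replace *and* with *or* between the two conditions, so that either one triggers the alert. Add one sentence saying that this trigger applies in both arms. Then verify that the live web system uses it.

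The cost is one word, one sentence and a configuration check. If the system turns out to run on *and*, the change may bring a few more alerts to handle. If it already runs on *or*, only the text changes.
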